### 8.5.6 EuroQol- 5 Dimension (EQ-5D-5L)

The EQ-5D-5L is a self-assessed, health-related, quality of life questionnaire. The scale measures quality of life on a 5-component scale, including mobility, self-care, usual activities, pain/discomfort, and anxiety/depression. Each level is rated on a scale that describes the degree of problems in that area (i.e., I have no problems walking about, slight problems, moderate problems, severe problems, or unable to walk). This tool also has an overall health scale where the rater selects a number between 1-100 to describe the condition of their health, 100 being the best imaginable. (*See Appendix H for a copy of The EQ-5D-5L*).

### 8.5.7 MoCA ( Montreal Cognitive Assessment)

The Montreal Cognitive Assessment is a rapid screening instrument for working memory, visual-spatial abilities, executive function, attention, concentration, language, and orientation. The total score ranges from 0 to 30; a score of 26 or above is considered normal, 18-25 = mild cognitive impairment (MCI), 10-17= moderate cognitive impairment (Alzheimer's disease) and less than 10= severe cognitive impairment. MoCA will be administered at the screening visit and at the final visit by the principal investigator (*See Appendix C for a copy of the MoCA*).

### 8.5.8 UPSIT (University of Pennsylvania Smell Identification Test)

The University of Pennsylvania Smell Identification Test is a comprehensive 40-item self-administered olfactory test that provides an absolute indication of smell loss (anosmia; mild, moderate, or severe microsmia). The kit consists of four booklets, each containing ten questions with a total score of 40. The score is compared to scores in a normative database from 4000 normal individuals (according to their age group and gender).

### 8.5.9 C-SSRS (The Columbia Suicide Severity Rating Scale)

The Columbia–Suicide Severity Rating Scale (C-SSRS) is an assessment tool that evaluates suicidal ideation and behavior. It rates an individual's degree of suicidal ideation on a scale, ranging from "wish to be dead" to "active suicidal ideation with specific plan and intent". A study member will conduct the assessment at screening using the Lifetime/Recent version and the Since Last Visit version at each safety/clinical visit. (*See Appendix I and J for the Lifetime/Recent version and the Since Last Visit version of the C-SSRS*).

### 8.5.10 Geriatric Depression Scale Short form (GDS-SF)

The Geriatric Depression Scale Short form (GDS-SF) is a 15-item screening tool that is used to identify depression in older adults. A score of 0 to 5 is normal. A score greater than 5 suggests depression. (*See Appendix K for a copy of the Geriatric Depression Scale Short form*)

### 8.5.11 Parkinson Anxiety Scale (PAS)

The Parkinson Anxiety Scale (PAS) is an anxiety measure scale for use in PD patients. This is a

12-item patient-rated scale with three subscales, subscales for persisting anxiety (5 items), episodic anxiety (4 items), and avoidance behavior (3 items). Items are a score on a 5-point Likert scale, with 0 = not or never, 1 = very mild or rarely, 2 = mild or sometimes, 3 = moderate or often and 4 = severe or almost always (*See Appendix L for a copy of The Parkinson Anxiety Scale*).

### 8.5.12 RBD-Single-Question Screen (RBD1Q)

Consists of a single question, answered “yes” or “no,” as follows: “Have you ever been told, or suspected yourself, that you seem to ‘act out your dreams’ while asleep (for example, punching, flailing your arms in the air, making running movements, etc.)?”

A positive answer is suggestive of REM Behaviour Disorder (RBD). RBD1Q can detect RBD with 94% sensitivity and 87% specificity (*See Appendix M for a copy of the RBD-Single-Question Screen*).

## 8.6 Donor-specific antibodies (DSAs)

As these MSC are derived from third party donor cells, we cannot discount the possibility of generation of recipient anti-donor alloimmune responses. The donor MSC will be haplotyped to determine the HLA gene expression on these cells before they are injected. In order to monitor the development of immune response directed against the donor MSC, we will perform Donor-specific antibodies in between infusions and 6 months and 12 months after the final infusion. HLA antibody level will be assessed using One Lambda (West Hills, CA) LABScreen Single Antigen Bead (SAB) Assay evaluated on either a Luminex 200 or LabScan 3D (instruments correlated for clinical use). The development of alloantibody directed against donor MSC will be identified by a positive response post-MSD injection. In case of sensitization patients will enter a modified schedule for their infusions (*As detailed in section 11.2.1*)

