Our collaborators at the University of Texas Health Science Center have demonstrated the safety and tolerability of intravenously administered MSCs in a pilot study of patients with recent ischemic stroke, and we demonstrated an overall effect of MSC infusion on limb function in PD animal models. In 2015, our research group obtained an IND to study the safety and tolerability of intravenous administration of bone marrow-derived MSCs in patients with mild to moderate PD. This Phase I study demonstrated that a single IV infusion of MSCs is safe, well-tolerated, and not immunogenic at doses that range from 1 to 10 X 10^6 IV MSCs/kg in subjects with mild to moderate PD. The most significant change in peripheral inflammatory markers steadily declined after 3 months with some residual effect at 6 months; based on this data, we would like to test 2 infusions vs. 3, at 4 month intervals for primary effect at 62 weeks and total follow-up at 88 weeks.

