### **3.5 Safety and Tolerability**

Monitoring for safety after administration of undifferentiated MSC focus on acute hypersensitivity reaction and a sub-acute or delayed antibody-mediated reaction that can occur within 3-4 weeks of the infusion. A primary concern, although extremely rare, in MSC infusion therapy is the development of a hypersensitivity reaction. Transient (lasting several hours) fever is the most common but again rare administration side effect. An acute, more serious hypersensitivity reaction causing fever, confusion, kidney, liver, or other organ damage, hemolytic anemia or pneumonitis has a very low risk of occurrence. Additionally, the systemic or intravenous route of administration means that the MSC can be distributed to many different tissues and organs in the body and we know that most will end up in pulmonary tissue and that the small molecules will distribute throughout the circulation.

The immune privileged status of MSC has been demonstrated using expanded undifferentiated and differentiated MSC *in vitro* culture. The cell surface of these cells expresses intermediate levels of human leukocyte antigen (HLA) major histocompatibility complex (MHC) class I molecules and negligible levels of HLA class II and Fas ligand. There is no expression of the co-stimulatory molecules B7-1, B7-2, CD40 or CD40L, and when exposed to allogeneic lymphocytes, they fail to elicit a reactive response. However, with alloantibody production following repeated doses of MSC, no life-threatening host vs. graft responses have been reported.

Lalu *et al* reviewed the safety of systemic MSC administration in humans in a meta-analysis of 36 studies. Based on these analyses, MSC therapy appears safe with transient fever as the only significant administration side effect.

To prove the safety and feasibility of the use of intravenously deliver allogeneic bone marrow-derived MSCs in patients with PD, our group designed and conducted the first USA single-center open-label dose-escalation phase 1 study and we demonstrated that a single infusion of allogeneic

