    - Diffusion-weighted MRI (for DTI analysis): will be used to examine white matter microstructures, which represent the structural pathways linking specific cortical and subcortical regions. Specifically, we expect to find increased fractional anisotropy and decreased mean diffusivity along white matter fibers that link regions exhibiting increased functional connectivity such as substantia nigra and dorsal striatum.
    - Neuromelanin MRI: neuromelanin-sensitive and iron-sensitive MRI sequences can robustly detect and quantify the neuromelanin loss, and iron accumulation in the substantia nigra pars compacta (SNc) and locus coeruleus (LC). We expect no changes in the neuromelanin (NM) signal in the SNc at 40 weeks.
  - Peripheral responses: serum or plasma concentrations of cytokines, chemokines, growth factors, and neurotransmitters will be measured at each follow-up and compared to baseline. Preliminary data generated in our laboratory demonstrated that MSCs effect likely relies on peripheral immune modulation, promoting an anti-inflammatory state.
  - Alpha-synuclein oligomers: Total and phosphorylated alpha-synuclein in plasma will be measured using ELISA and total alpha-synuclein in CSF will be measured using Protein Misfolding Cyclic Amplification (PMCA). Kinetic parameters seem to correlate with disease severity measured by H&Y.

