## 10. Study schedule

The study will last a total of one year and 8 months (88 weeks) per patient (3 groups) and will include 11 clinical visits and 10 telephone evaluations (*Please see section 10.3 for the study timeline and 10.4 for study schedule*).

There are 6 types of clinical visits: Screening, Baseline, Infusion, Safety and Clinical assessment, unscheduled visit, and final visit plus phone call evaluations starting after the first infusion.

- Visit #1 Screening Visit (between week -12 to week -3): after signing the consent and discussing the purpose and timeline of the study, the PI will confirm the PD diagnosis and establish the current disease stage. At this visit, the CRU staff will collect blood for laboratory assessment. The purpose of this visit is to ensure that the patient meets the inclusion and exclusion criteria.
- Visit #2 Baseline visit (between week -11 to week-1): the purpose of this visit to obtain baseline measurements on serum, plasma, CSF, and neuroimaging.
- Visit #3 Infusion Day (week 0): First IV MSCs infusion.
- Visit #4 Clinical and Safety assessment (week 9+/-1.5 week): the purpose of this visit is to determine the safety and the immediate immunological, physical and neurological response to the first infusion.
- Visit #5 Infusion Day (week 18+/-1 week): Second IV MSCs infusion.
- Visit #6 Clinical and Safety assessment (week 27+/-1.5 week): the purpose of this visit is to monitor safety and the immunological, physical and neurological response to the second infusion.
- Visit #7 Infusion Day (week 36+/-1 week): Third IV MSC infusion
- Visit #8 Clinical and Safety assessment (week 40+/-1.5 week): the purpose of this visit is to monitor the safety and the immunological, physical and neurological response to the third infusion. Additionally, to collect enough data for our first interim analysis.

- Visit #9 Clinical and Safety assessment (week 49+/-1.5 week): the purpose of this visit is to monitor the safety and the immunological, physical, and neurological response to the infusions.
- Visit #10: Clinical and Safety assessment (week 62+/-1.5 week): the purpose of this visit is to monitor the safety and the immunological, physical, and neurological response to the infusions.
- Visit # 11: Final visit (week 88+/-1.5 week): the purpose of this visit is to determine the physical and neurological response to the complete MSC treatment.

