- Provide PDQ-39 (Parkinson's Disease Questionnaire) for self-administration. (All visits except visit 9)
- Collect blood samples for:
  - DSA (Donor specific antibodies). Order as HLA typing. (**All visits except visit 9 & 10**)

- Peripheral markers: Neurotransmitters, Oxidative stress, cytokines, chemokines, and growth factors. (*All visits except visit 10*)
- $\alpha$ -synuclein oligomers levels. (*Only at visit 8 & 9*)
- Performed Neuroimaging in the levodopa OFF state (*Only at visit 8*):
  - High-resolution T1- & T2-weighted MRI.
  - Perfusion MR.
  - Diffusion-weighted MRI.
  - Neuromelanin MRI.
- Performed Lumbar Puncture and observe for 2 hours (*Only at visit 9*)
- Collect urine sample for  $\alpha$ -synuclein oligomers (*Only at visit 9*)
- CSF samples for:
  - CBC with differential.
  - Glucose and Protein levels
  - $\alpha$ -synuclein oligomers
  - Markers: Neurotransmitters, Oxidative stress, cytokines, chemokines, and growth factors.
- Review DSA results from the previous visit. (*Only at visit 4 & 6*):
- Assess the Need for change in symptomatic therapy.

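### The 6-month donor-antibody sample promised in section 8.6, and the peripheral markers promised at each follow-up in 5.1.2, are not scheduled at week 62 (Visit 10)

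*Protocol*

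**What the plan says.** Two sections of the Protocol set out what will be sampled:

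- Section 8.6, on donor-specific antibodies (DSA): "we will perform Donor-specific antibodies in between infusions and 6 months and 12 months after the final infusion".
- Section 5.1.2, on peripheral responses: "growth factors, and neurotransmitters will be measured at each follow-up and compared to baseline".

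The timing comes from section 10: "Visit #7 Infusion Day (week 36+/-1 week): Third IV MSC infusion". The synopsis gives every subject three infusions, so this date is common to all arms. Section 10 places Visit 10 at week 62 ± 1.5 and Visit 11 at week 88 ± 1.5, and lists monitoring of the immunological response among the purposes of Visit 10. The schedule table puts Visit 10 in the follow-up period.

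The operational text differs. In the list of procedures for the clinical and safety visits (section 10.1.4), DSA is drawn at "All visits except visit 9 & 10" and peripheral markers at "All visits except visit 10". Blood for alpha-synuclein is limited to Visits 8 and 9. In the schedule table the rows for CBC and metabolic panel, peripheral markers, plasma alpha-synuclein and DSA are all blank at week 62.

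**The concern.** One part of the Protocol commits to a sample that another part instructs the site not to take. Sites work from the visit list and the schedule table, and these agree with each other, so the sample will not be drawn. No analysis plan can recover a sample that was never collected.

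Two things are at stake. First, DSA compared with baseline is a named secondary safety outcome in 5.1.2, in a trial whose objective includes choosing the safest number of repeat doses. A response that appears after the week-40 draw and is gone by week 88 would be recorded as no response. Second, section 3 bases the dosing interval on Phase I marker changes that "steadily declined after 3 months with some residual effect at 6 months". With no blood at week 62, this trial cannot show whether a marker effect is still present 6 months after the last infusion.

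**Working it through.** The Protocol gives no figure to reproduce. The check is visit arithmetic, set beside the sampling lists.

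**Inputs.** Third infusion at week 36 ± 1; Visits 8, 9, 10 and 11 at weeks 40, 49, 62 and 88, each ± 1.5 (section 10). Sampling from 10.1.4, 10.1.5 and the schedule table.

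**Time since the final infusion** = visit week − 36, at about 4.345 weeks per month:

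| Visit | Week | Weeks after infusion 3 | Months | DSA | Markers |
|---|---|---|---|---|---|
| 8 | 40 | 40 − 36 = 4 | 0.9 | yes | yes |
| 9 | 49 | 49 − 36 = 13 | 3.0 | no | yes |
| 10 | 62 | 62 − 36 = 26 | 6.0 | no | no |
| 11 | 88 | 88 − 36 = 52 | 12.0 | yes | yes |

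With windows, Visit 10 falls between 60.5 − 37 = 23.5 and 63.5 − 35 = 28.5 weeks after the infusion (5.4 to 6.6 months). It is therefore the 6-month visit anywhere in its window. No other scheduled visit is near 6 months. The 12-month DSA in 8.6 is scheduled; the 6-month one is not.

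**Longest gap between draws after the third infusion, as written:**
- DSA: 88 − 40 = 48 weeks (86.5 − 41.5 = 45 to 89.5 − 38.5 = 51 with windows).
- Markers: 88 − 49 = 39 weeks.

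**With both samples added at week 62:**
- DSA at weeks 40, 62 and 88: gaps 22 and 26, longest 26 weeks.
- Markers at weeks 40, 49, 62 and 88: gaps 9, 13 and 26, longest 26 weeks.

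**Do other readings remove the conflict?**
- *Different visit dates.* Appendix E lists Visits 10 and 11 at weeks 52 and 78, and Appendix O implies a third infusion at about week 26. Then 52 − 26 = 26 and 78 − 26 = 52, so Visits 10 and 11 are still the 6- and 12-month visits.
- *Final infusion read as the last active one in the two-infusion arm.* The position of that arm's placebo infusion is not stated. If the last active dose were at week 18, 6 months would be about week 18 + 26 = 44, with the nearest DSA at week 40 (22 weeks). Twelve months would be week 18 + 52 = 70, with no matching DSA. The conflict moves but stays.
- *Early termination visit.* It includes both samples and could fall near 6 months by chance, but it is not a scheduled value.

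**The case against.** The strongest reply is that conduct is unambiguous. The exceptions for Visit 10 are explicit and appear in both the text and the table, so they look deliberate, and 8.6 and 5.1.2 may simply be the sections in error. Section 5.1.2 refers to follow-up in general and does not name 6 months. All infusions are finished by week 62, so no dosing decision depends on the sample. DSA is still drawn at baseline and at weeks 9, 27, 40 and 88, and a persistent antibody would be seen at week 88. The only human DSA result in the document, from Phase I, shows no response to donor HLA over 12 months, though after a single infusion.

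Much of this stands. It limits the consequence and leaves open which section should change. It does not remove the conflict, because 8.6 names the 6-month sample and week 62 is a follow-up visit under 5.1.2.

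A reader might infer more, which the documents do not support:

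- *That Hypothesis 3.1 loses its mediator.* A mediator should precede its outcome, and markers at weeks 9, 27, 40 and 49 all precede the week-62 motor score. Only the concurrent value is missing.
- *That markers after the last infusion are sampled only at 3 months.* They are drawn at about 4, 13 and 52 weeks.
- *That the week-40 DSA comes too early.* Section 3.5 describes "a sub-acute or delayed antibody-mediated reaction that can occur within 3-4 weeks of the infusion". The nominal lag is 4 weeks; a lag of 38.5 − 37 = 1.5 weeks needs the latest permitted infusion and the earliest permitted visit. Section 3.5 concerns a clinical reaction, adverse-event contacts are set for weeks 38 and 44, and a week-62 draw would not help with that period.
- *That the gap favours the three-infusion arm.* All arms share one DSA schedule, and the Protocol gives neither antibody kinetics after repeat dosing nor the position of the placebo infusion in the two-infusion arm.

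**Conclusion.** The point holds as an internal contradiction that costs data. Sections 8.6 and 5.1.2 commit to samples that 10.1.4 and the schedule table exclude at Visit 10. If the visit schedule is followed, no subject has a scheduled DSA or peripheral-marker value 6 months after the final infusion. The unsampled intervals are 48 weeks for DSA and 39 weeks for markers.

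This rests on the final infusion being the third, at week 36 in every arm, and on 6 months being 26 weeks. The other readings tested above leave a mismatch.

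The consequence is bounded. A donor-antibody response confined to the period between weeks 40 and 88 would be missed; how likely that is cannot be judged from the Protocol. Although week 62 is also the primary-endpoint visit, the primary endpoint is unharmed: the MDS-UPDRS motor score is scheduled there. The matter deserves correction because the loss is certain under the present schedule, cannot be made good at analysis, and is cheap to avoid.

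**What to change.** Reconcile 8.6 and 5.1.2 with 10.1.4 and the schedule table, in one of two ways:

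1. **Collect the samples.** Remove Visit 10 from the DSA and peripheral-marker exceptions in 10.1.4, mark both rows at week 62 in the schedule table, and state that the week-62 DSA enters the immunologic safety outcome. This delivers what 8.6 and 5.1.2 state and brings the longest gap to 26 weeks for both. The cost is one blood draw per patient (at most 45 treated subjects) at a visit they already attend, assays that the plan already commits to, and an amendment. No extra visit is needed.
2. **Correct the statements.** If the sponsor does not intend these samples, 8.6 should list the DSA time points actually drawn, 5.1.2 should name the visits with marker samples, and no 6-month DSA or marker result should be claimed. This costs only an amendment, but the 6-month data are given up.

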## 8.7 Peripheral markers

Serum and plasma samples will be stored at  $-80^{\circ}\text{C}$  until further analysis. To determine the proposed biological markers listed in *Table 3*, a Millipore Milliplex MAP® 37-plex human cytokine/chemokine panel and Milliplex MAP Human Neurodegenerative Disease Magnetic Bead Panel 3 (EMD Millipore, Billerica, MA, USA) will be used.

**Table 3. Peripheral and CNS Molecular Markers**

| Growth Factors   | Inflammation                                                  | Chemotaxis                                                                                     | Lymphocytes                              | Neurotransmitters & metabolites        | Oxidative stress markers   | Physiological Markers |
|------------------|---------------------------------------------------------------|------------------------------------------------------------------------------------------------|------------------------------------------|----------------------------------------|----------------------------|-----------------------|
| VEGF, BDNF, GDNF | IL-1 $\beta$ , IL-2, IL-6, IL-17, TNF $\alpha$ , COX-2, PGE-2 | CCL2 (MCP-1), CCL7 (MCP-3), CCL11 (Eotaxin), CCL22 (MDC), CXCL10 (IP-10), CX3CL1 (Fractalkine) | IFN $\gamma$ , TGF $\beta$ , IL-4, IL-10 | 5-hydroxytryptamine, Homovanillic acid | Total antioxidant capacity | NfL, mir-7            |

## 8.8 Lumbar Puncture

The same biological markers, as proposed in the peripheral markers, will be assessed in the spinal fluid at baseline and week 49. A qualified neurologist will perform a bedside lumbar puncture under sterile procedural guidelines; approximately 15-20 ccs of CSF will be collected and will take approximately 30-60 minutes. Afterward, the subject will remain recumbent and in observation at the clinical research unit (Part of the Memorial Hermann hospital) for 2 hours following the procedure, with fluid intake encouraged.

## 8.9 Peripheral CSF and urine $\alpha$ -synuclein oligomers:

CSF, plasma and urine will be used to assess peripheral  $\alpha$ -synuclein oligomers. Total and phosphorylated alpha-synuclein in plasma will be measured using ELISA and Total alpha-synuclein in CSF and urine will be measured using Protein Misfolding Cyclic Amplification (PMCA). There is published data stating that when preformed  $\alpha$ -synuclein aggregates are incubated with MSC-conditioned medium,  $\alpha$ -synuclein aggregates become disassembled, and insoluble and oligomeric forms of  $\alpha$ -synuclein are markedly decreased. In addition, kinetic parameters correlated with disease severity measured by H&Y.

## 8.10 Neuroimaging

We will include 3 imaging time points per patient, baseline, week 40, and week 88.

Imaging will be collected using a 3 tesla Philips Ingenia MR scanner. A T1-weighted magnetization-prepared rapid acquisition turbo field echo sequence will be collected (repetition time/echo time TR/TE] = 8.4/3.9 ms; flip angle = 8 degrees; matrix size = 256  $\times$  256; field of view = 240 mm; slice thickness = 1.0 mm, sagittal acquisition). A T2-weighted turbo spin-echo volume acquisition (TR/TE = 2500/367 ms; echo train length 120, pixel bandwidth 380, flip angle = 90 degrees, matrix size = 256  $\times$  256; field of view = 240 mm, slice thickness = 0.94 mm, 186 sagittal slices) will also be collected. A fluid-attenuated inversion recovery (FLAIR) volume will also be collected (repetition time/echo time TR/TE = 4800/323 ms; inversion time = 1650 ms; echo train length = 182; pixel bandwidth = 957; flip angle = 90 deg; matrix size = 256  $\times$  256; isotropic 1 mm voxels). Detailed structural MRI analysis will be carried out according to Ellmore et al 2010^148.

- **Perfusion MRI:** We will measure resting cerebral blood flow (CBF) using a pseudo-continuous arterial spin labeling (pCASL) MRI sequence with gradient-echo echo-planar

imaging (EPI). Arterial spin-labeled (ASL) perfusion MRI allows for noninvasive quantification of CBF as part of a multimodal MRI examination. It is less invasive, less costly, and more widely available than radionuclide methods like Xe-133 clearance or O positron emission tomography. Critical parameters our acquisition protocol include the following TR/TE = 4000/17 msec, flip angle = 90 degrees, slice thickness = 5 mm, 240 mm field of view, slice gap = 1.0 mm, voxel resolution = 2.75x2.75x6 mm^3, 30 dynamic signal averages, with a labeling duration of 1650 msec and a post-labeling delay of 1600 msec. ASL data processing and CBF calculation will be performed in AFNI. Raw ASL images will be co-registered to each subject's high-resolution T1-weighted MRI. The T1 MRI will be segmented into gray, white, and CSF binary masks and sampled to the resolution of the raw ASL images. After motion correction, the ASL images will be multiplied by the gray and white matter masks, and global cortical gray matter and white matter images will be generated. Pairwise subtraction images (label minus control) will be generated for each dynamic after smoothing by an 8 mm full-width half-maximum kernel. Averaged difference images will be converted to ml/100g/min gray matter and white matter CBF maps using a single-compartment model .

- **Diffusion-weighted MRI (for DTI analysis):** A set of diffusion-weighted image volumes (32-directions, high angular resolution) will be collected using the gradient overplus option with one B0 (non-diffusion weighted) image volume acquired before the acquisition of one repetition of the diffusion-weighted scans (TR/TE = 8500/67 ms; FA = 90 deg; matrix size 128 x 128; FOV = 224 mm; 2 mm thick axial slices, b-value of 800 s/mm^2). Diffusion tensor and associated computations will be done as specified in Ellmore et al. 2014. Diffusion tensor imaging will be used to examine white matter microstructures, which represent the structural pathways linking specific cortical and subcortical regions.
- **Neuromelanin MRI:** We will use a 2D gradient response echo sequence with magnetization transfer contrast (2D GREMT) with the following parameters: repetition time (TR) = 260 ms; echo time (TE) = 2.68 ms; flip angle = 40°; in-plane resolution = 0.39 × 0.39 mm^2; partial brain coverage with field of view (FoV) = 162 × 200; matrix = 416 × 512; number of slices = 10; slice thickness = 3 mm; slice gap = 0 mm; magnetization transfer frequency offset = 1,200 Hz; number of excitations (NEX) = 8; acquisition time = 8.04 min. The slice-prescription protocol will consist of orienting the image stack along the anterior-commissure–posterior commissure line and placing the top slice 3 mm below the floor of the third ventricle, viewed on a sagittal plane in the middle of the brain. This protocol will provide coverage of SN-containing portions of the midbrain (and cortical and subcortical structures surrounding the brainstem) with high in-plane spatial resolution using a short scan easy to tolerate by clinical populations. Whole-brain, high-resolution structural MRI scans will also be acquired for preprocessing of the 2D GRE-MT (NM-MRI) data: a T1-weighted 3D BRAVO sequence (inversion time = 450 ms, TR ~ 7.85 ms, TE ~ 3.10 ms, flip angle = 12°, FoV = 240 × 240, matrix = 300 × 300, number of slices = 220, isotropic voxel size =

0.8 mm^3) and a T2-weighted CUBE sequence (TR = 2.50 ms, TE ~ 0.98 ms, echo train length = 120, FoV = 256 × 256, number of slices = 1, isotropic voxel size = 0.8 mm^3).

The anatomical imaging (T1- and T2- weighted and Fluid Attenuated Inversion Recovery) data allow us to see brain structure at the level of about 1 cubic millimeter. We will use these scans to estimate the volume of subcortical structures (e.g., putamen, caudate nucleus) to measure the cortical thickness (e.g., gray matter density), and detect any gross structural changes or inflammation that appear during treatment. These structural MRI scans are also necessary to provide co-registration templates (to correct for movement between scans) for the ASL, DTI, and neuromelanin sequences described above.

